### Economic analysis

The utilisation of healthcare cost will be calculated by applying a standardised unit cost allowing the evaluation of cost development for each group over time. The costs of healthcare utilisation (months 6 and 12) will be analysed using appropriate regression models. Intervention type, trial site and utilisation costs at baseline will be included as the independent variables.

In the second step, cost-effectiveness analyses of the intervention will be conducted from the healthcare perspective. Therefore, the development of the different endpoints will be analysed in relation to the costs of healthcare utilisation and the costs of the intervention. Incremental cost effectiveness ratios and the corresponding confidence intervals will be estimated.

## Methods: independent committees

### Data monitoring committee (DMC)

A DMC comprises four specialists with high expertise in conducting clinical trials in Tai Chi and EYT and in safety assessment and falls in the elderly. These specialists are independent from the study organisers and all trial sites. They will regularly review the complications of the trial treatments and advise the principal investigator (the details are described in the DMC charter).

### Public and patient involvement

The PPR are involved during the planning, conduction and analysis of the trial following the recommendations by INVOLVE (http://www.invo.org.uk). Through this, the views, values, needs, strengths and limitations of the older people are integrated. In the personal semi-standard interviews, the details of the trial design are explained and discussed. Their comments and recommendations centre on motivation; how to recruit older people, elderly leading a reclusive life and people from a lower socioeconomic background; and the importance of an appreciating, encouraging and calm atmosphere, the giving of sufficient time and avoiding the sense of being in need of help. Audio-visual material to support practicing at home is also recommended. Therefore, communication training, the provision of audio-visual material and the details of the recruitment strategy are added, and more time is planned for the visits. The PPR are invited to all relevant trial meetings and receive relevant trial documents, analyses and trial reports. Particularly, the documents handed out to participants (i.e. brochure, audio-visual material, information sheets, flyer and web page information) and their adequacy, comprehensibility and readability are discussed in detail. The PPR will be informed about the progress of the trials and unexpected problems and will be consulted regarding participant recruitment.

## Methods: ethics and dissemination

### Ethical and legal principles

Before enrolment, the potential participants will be informed about the goals, procedures and possible risks of the trial; data protection and confidentiality; and the voluntary nature of the participation throughout the study. A written informed consent must be obtained for all potential participants before they are registered. Before the study begins, approval from the local ethic committees will be obtained. (From the Ethics Committee of the University of Freiburg, the ethical approval has been obtained: 183/19; 23.07.2019, as well as from the Ethics Committees of Tübingen for the sites Tübingen and Filderstadt, 561/2019BO1, 21.10.2019, Witten/Herdecke 150/2019, 31.07.2019 and Ulm 284/19, 01.08.2019; Berlin relies on the vote from Freiburg). The study will be carried out in compliance with the Declaration of Helsinki and the ICH-GCP.

### Confidentiality

Data protection follows the data protection concept of the CTU and must be fully and permanently complied with. The names of participants are only available in the source documents, which are kept in a secure and lock-protected location at the trial sites and in the participation lists of the EYT therapists and Tai Chi teachers. The findings obtained in the course of the study will be stored in electronic media and treated in strict confidence. For the protection of these data, organisational measures are taken to prevent disclosure to unauthorised third parties. For example, the subject data will be captured in pseudonymised form (i.e. subject ID number for the particular study and year of birth) throughout the documentation and evaluation phases.

### Ancillary care

The participants enrolled in the trial are included in an insurance that covers the expenses in case a participant suffers harm from trial participation.

### Access to data and dissemination policy

The principle investigator has full access to the final trial dataset. The trial results, treatment manuals and videos will be published and presented to healthcare professionals, the public and other relevant interest groups. The full trial protocol is accessible by the public (see Supplementary file 5). The principle of open data is supported (https://www.bihealth.org/de/quest-center/mission-ansaetze/open-science). Anonymised data may be shared with cooperating scientists or scientists who have other medically or scientifically well-founded reasons (goals referring to transparency, replicability, different analyses, combinations and meta-analyses of data). Their research must aim at improving the care of elderly people, and the researchers have to ensure data protection.​.

## Discussion

Falls are a major threat for elderly people, and they usually mark the end of their independence [6]. About 80% of women aged 75 or older prefer death to a ‘bad’ hip fracture, which can result in loss of independence and nursing home admission [62]. Falls, even if non-injurious, lead to a decline in social activities, mobility, and cognitive and physical performance [63, 64]. In European countries, North America and Australia, 0.85–1.5% of the total national healthcare expenditures are spent on fall-related costs, which correspond to 0.07–0.20% of the gross domestic product [65]. Therefore, reducing the risk of falls and fear of falling and increasing mobility, physical fitness and activity can be a significant benefit for elderly people, providing them with functional independence, autonomy and better life quality and reducing morbidity, costs and healthcare utilisation.

This work is the first trial investigating EYT in elderly people with high risk of falling. We expect the effects of EYT on falls to be similar to the effects of Tai Chi, but to be different with regard to preferences, memorability of exercises, adherence, mood and quality of life. The patient’s perspective, treatment context and adaptability to physical fitness are important for motivation [19–21]. Although Tai Chi has been frequently investigated internationally, this trial is the first trial to examine Tai Chi in Germany in this population and indication.

The strengths of the ENTAiER trial lie in the highly relevant issues of aging population, increasing burden of mostly lifestyle-related multimorbidity and high risk of falls increasing morbidity, mortality and costs; the methodological rigor, the multi-disciplinary team and its high competence and experience; and the data quality and conformity to the ICH-GCP. Moreover, the active and constant involvement of the PPR improved the trial quality and its consequent adjustment to patients’ needs, values, goals and capabilities. Transparency is highly valued in this study. Aside from the PPR, the design has been discussed with many experts in the field, organisations representing or supporting senior citizens and healthcare providers. The treatment manuals and videos will be published after the termination of the trial to enable replicability or to implement them in future care. They further enable the autonomy of participants for independent practicing beyond group classes. We attempt to enrol older people who lead a reclusive life, are economically disadvantaged and have an increased risk of falling [51] but seldom visit exercise classes or other activities of their own accord. The participation of these people is supported by a specific motivational concept and by an appreciating and non-judgmental communication through the study personnel, teachers and therapists.

The ENTAiER trial has some limitations. First, the focus of the trial tends towards a pragmatic assessment at the expense of explanatory interpretation. Therefore, the result will assess the combination of exercises and teachers’/therapists’ ability to instruct, motivate and individually tailor exercises. The differences between therapists cannot be captured. However, more than 20 therapists and 20 teachers in different settings (trial sites, places for group settings and groups) will provide EYT and Tai Chi, levelling out the effects of specific personalities and settings. We will also monitor the adherence to home and group training, the adherence to and adaption of exercises by the therapists and teachers, the participants’ subjective impression of what motivated them and the inner coherence with practices.

No blinding is possible for exercise classes, and no intervention mimicking EYT or Tai Chi while lacking any specific effects for fall prevention can be found. Potential competing interventions, such as stretching, life reviewing groups and training in health competencies and literacy, if well designed and conducted, all have specific effects on the risk factors related to falls. However, if they are clearly designed to lack all specific effects on any risk factors, then they are ethically questionable, and the PPR voted against them. A waiting list control has been discussed to have nocebo effects, leading to an overestimation of the effects [66]. Therefore, a three-arm design, which compares a highly investigated versus a scarcely investigated intervention versus a standard care only group, is chosen.

We may document more complications in the EYT and Tai Chi groups in comparison with the control group in case the participants in the intervention groups practice more often and more intensely. Therefore, more untoward medical events may be potentially linked to the exercises. We reduce this bias by presenting open questions and avoiding any influence through suggestive questions. Furthermore, we would be more concerned by an underreporting of potential complications, which is not to be expected. The net risk necessitating the medical and non-medical services (FIMA) will be regularly assessed without risk of bias.

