#### What

EYT [30, 31] and Tai Chi [22–25] exercises are described in a manual. They are derived from previous studies investigating fall prevention or based on recommendations by experts. They have been reviewed by Tai Chi teachers, EYT therapists and external experts.

‘Standard Care’: participants receive a well-described brochure that recommends evidence-based measures to reduce risk of falling (e.g. training balance, strength, flexibility, endurance; medication modification; safe home environment; bone health; safe footwear; assistive devices) and provides addresses for more information or support [38]. Participants will also be recommended to visit their primary care physician to receive care based on evidence-based guidelines to prevent falls [39] or to manage multi-morbidity [40] or polypharmacy [41].

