### Complications

The complications that can arise from EYT, Tai Chi or other exercises will be collected monthly. A complication is any untoward medical occurrence such as any unfavourable and unintended sign, symptom, or disease that is possibly related to the study intervention. Not regarded as complications are conditions that were already present at the time of the informed consent or aching muscle, which is to be expected. Starting with the open questions, participants are asked about any untoward medical occurrences or unplanned medical visits. In case of a possible relation to the intervention, these occurrences are documented, including severity and outcome. Moreover, therapists or teachers can inform the trial sites about the complications. Falls and injurious falls are documented as primary outcomes, and injuries are reported as complications in case they occurred during training. Further information on safety will be derived from the FIMA, which assesses healthcare utilisation such as physician contacts and hospitalisations.

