### Blinding and minimising risk of bias

The blinding of the Tai Chi and EYT group and the standard care group to their allocation is not possible because it is obvious in which group the participants are randomised, as all three trial interventions differ substantially. The outcomes are either directly reported by the participants (falls, questionnaires) or in close communication with the participants (falls, complications, BBS, MoCA, IADL). Therefore, also a reliable blinding of the outcome assessment to participant allocation is not possible. Outcome assessors are instructed by a written guide to start with open and general questions and to avoid mentioning the group allocation as long as possible. Since the electronic case report forms differ depending on randomized treatment, the statistical analysis will not be blinded, but all confirmatory analyses are prespecified in the clinical trial protocol and decisions on analysis data sets will be finalized without access to the unblinded data. Concealment of the randomisation will be guaranteed to minimise selection bias. All assessments will be conducted in a comparable setting and time. The primary outcome parameter is clearly defined and described in detail [42]. The combination of prospective, daily, participant-completed falls diary and monthly calls is regarded to be reliable and captures most of the falls among seniors [55]. To reduce incomplete outcome data, travel costs for public transportation are refunded, and the trial sites may conduct the follow-up visits at the participants’ home. Two of the groups receive interventions in a comparable setting, support and frequency. The third (control) group, although not offered regular training sessions, can still avail of such opportunities through the addresses in the brochure, the general courses in their city or their primary care physician. They receive human attention through an appreciating communication with the trained study personnel and their primary care doctors, other consultants and medical referrals at their discretion and informed by evidence. The patient informed consent (form) makes no remarks on the potential efficacy of EYT or Tai Chi to reduce expectancy bias. Publication bias will be reduced by study registration in the trial registers, the publication of the trial protocol and the results and the support of open data.

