## Methods: data collection, management and analysis

### Data collection methods

BBS, MoCA, IADL and the complications are assessed by the study personnel.

The FES-I, GDS-15, SF-12, ICPH and FIMA questionnaires, the falls and training diaries and the self-designed questionnaires (see Supplementary file 1, 2, 3 and 4) are filled in by the participants in the same environment, which is quiet and respectful of the subject’s privacy. As much as possible, the outcome measures are assessed at a consistent time of the day and consistent with the medication cycles, particularly in participants with conditions like Parkinson’s and multiple sclerosis. The data obtained by the investigators are kept in source documents and directly entered in a trial-specific electronic case report form (eCRF). The patient-reported questionnaires are stored as the participants’ source documents, and a duplicate is sent to the CTU in Freiburg to be entered in the eCRF.

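### Service use (FIMA) is presented as a bias-free measure of net risk, but it is unblinded self-report and counts contacts that are part of standard care

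*Protocol article*

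**What the plan says.** The limitations part of the Discussion accepts that more complications may be recorded in the exercise arms, because people who practise more have more events that could be linked to practice. Open questioning is given as one mitigation. The paragraph then closes with FIMA: "The net risk necessitating the medical and non-medical services (FIMA) will be regularly assessed without risk of bias". The Complications section gives the instrument its safety role: "Further information on safety will be derived from the FIMA, which assesses healthcare utilisation such as physician contacts and hospitalisations".

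Three other parts of the article bear on this.

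- Data collection methods: "The FES-I, GDS-15, SF-12, ICPH and FIMA questionnaires, the falls and training diaries" are listed among the instruments that "are filled in by the participants in the same environment".
- Blinding and minimising risk of bias: participants cannot be blinded because "it is obvious in which group the participants are randomised". The section names questionnaires among the outcomes that participants report directly, and concludes that outcome assessment cannot be reliably blinded either. It says the control group receives attention through study staff and "their primary care doctors, other consultants and medical referrals at their discretion and informed by evidence".
- Interventions: under What, standard care includes this element: "Participants will also be recommended to visit their primary care physician". Under Who provides, it is delivered by the primary care doctor or consultant.

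FIMA is also listed as a secondary outcome for use of medical and non-medical services, and healthcare utilisation feeds the economic analysis.

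**The concern.** FIMA is offered as the counterweight to a bias that the article admits in its complication counts. If the counterweight can itself be biased, the reassurance does not hold.

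There are two separate difficulties. First, the measure is self-report under known allocation, which the article's own blinding section treats as open to bias. Second, a physician contact is not only a consequence of harm in this trial. It may be the recommended fall-prevention visit, a referral, routine care of chronic disease, or treatment of an exercise injury. A total of contacts mixes these.

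At stake is the wording of the safety conclusion. Fewer services in an exercise arm could be reported as lower net risk, or more services as higher net risk, when the difference reflects care-seeking or reporting. A real excess of exercise-related visits could also be hidden by an opposite difference in other contacts.

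**Working it through.** **1. The claimed property against the design.** No arithmetic is needed for the main point.

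- Discussion: net risk from FIMA is free of bias.
- Data collection methods: participants complete FIMA.
- Blinding section: participants know their arm, questionnaires are directly participant-reported, and reliable blinding of outcome assessment is not possible.

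The first statement cannot stand beside the other two.

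**2. What FIMA does and does not avoid.** Under Complications, an occurrence is documented when a relation to the intervention is possible. FIMA needs no such judgement, so it escapes that attribution bias. It does not escape differential recall or reporting by arm, nor differences in the threshold for seeking care.

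**3. What is being counted.** FIMA includes physician contacts (Complications). These are the delivery route of standard care (Interventions) and part of a utilisation outcome (Outcomes). When collecting complications, staff ask about unplanned medical visits; the article draws no such distinction for the safety use of FIMA.

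**4. Illustration of size.** The article gives no service-use figure to reproduce. Its group size is the only design figure needed, and it reproduces. With 50%, 35% and 35% fallers, the mean is 0.40, the sum of squared deviations is 0.0100 + 0.0025 + 0.0025 = 0.015, and 155 × 0.015 / (0.40 × 0.60) = 9.69. As the noncentrality of a 2-df chi-square test at 5%, this gives power 80.2%. Randomising 550 gives 550/3, about 183 per arm.

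Assumptions, not from the documents: harm is equal in all arms; the share with at least one doctor contact is p in one arm and p + d in the other, for care-seeking or reporting reasons only; p is 30%, 50% or 70%.

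Chance of a two-sided 5% result in the direction of the gap = Φ[(d − 1.96·SE0)/SE1], where p̄ is the mean of the two shares, SE0 = √(2p̄(1−p̄)/n) and SE1 = √{[p1(1−p1) + p2(1−p2)]/n}.

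Worked case, p = 50%, d = 5 points, n = 183: SE0 = √(2 × 0.525 × 0.475/183) = 0.0522; SE1 = √((0.2475 + 0.25)/183) = 0.0521; (0.05 − 0.1023)/0.0521 = −1.00; chance 15.8%.

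| Base share | No gap | 5 points, n 155 / 183 | 10 points, n 155 / 183 |
|---|---|---|---|
| 30% | 2.5% | 15.3% / 17.4% | 45.4% / 51.8% |
| 50% | 2.5% | 14.0% / 15.8% | 42.4% / 48.5% |
| 70% | 2.5% | 16.5% / 18.7% | 52.9% / 59.9% |

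Swapping the arms gives the same figures. A gap upward in controls makes exercise look safer, and a gap upward in an exercise arm makes it look more harmful.

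**The case against.** The strongest reply is that the sentence should be read in its paragraph. The bias under discussion there is that more practice leads to more events being attributed to practice. FIMA records service use without any attribution, so it plausibly avoids that bias, and the sentence is then only loosely worded. This stands in part and belongs in the corrected text. It does not rescue an unqualified statement about a self-reported, unblinded measure.

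FIMA is also supplementary. The stated safety analysis is rates of adverse and serious adverse events with confidence intervals, complications are collected monthly and reviewed by the data monitoring committee, and injurious falls are a secondary outcome. The article specifies no significance test on FIMA for safety. This stands: a reader might infer that FIMA is the trial's main evidence of no net harm, but the documents do not give it that place.

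Two further readings are tempting and unsupported. One is that contacts differ between arms by design. They do not: all three arms receive standard care, and neither the recommendation to see the primary care doctor nor its row in Table 1 is limited to one group. Only uptake or reporting can differ. The other is that the bias favours the exercise arms. The description of the control group's care makes higher doctor use there plausible but does not show it, and regular contact with therapists could raise service use in the exercise arms instead.

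Finally, the rates in the illustration are assumed. That is correct, and the conclusion does not depend on them.

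**Conclusion.** The concern holds in this form: the article claims freedom from bias for a measure that its own design leaves open to reporting and care-seeking bias, and it does so while using that measure to offset a bias it admits elsewhere. A between-arm difference in total service use cannot by itself be read as a difference in net harm, in either direction.

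The contradiction rests on the article's own statements alone. The size is illustrative: with about 183 per arm and base shares of 30–70%, a 5-point gap unrelated to harm gives a nominally significant result in the direction of the gap in 16–19% of trials, and a 10-point gap in 49–60%, against 2.5% with no gap. Because FIMA is additional safety information, the consequence is confined to how that information is described and interpreted. The adverse event analysis and the efficacy analyses are unaffected.

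**What to change.** In the Discussion, replace the bias-free claim with a statement that FIMA is unblinded, self-reported utilisation; that it avoids the judgement of relatedness to the intervention; and that it does not avoid reporting or care-seeking bias.

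In Complications, state that a between-arm difference in total service use will not be interpreted as a difference in net harm. In the safety reporting, show hospital admissions separately from physician contacts and keep both. Admissions are less discretionary, though still self-reported here. Dropping physician contacts would remove exercise injuries treated in outpatient care from this source.

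The cost is two wording changes and one extra split of a table from data already collected. The downside is a less favourable statement about the supplementary safety data.
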